### Participants

Twenty schools will be identified and recruited in conjunction with Gwynedd Education Services.

In total 240 children will participate (120 intervention, 120 control) across the 20 schools. The 240 children, aged 4-8 years will be identified as scoring at least borderline for concern on the total difficulties score of the Teacher Strengths and Difficulties Questionnaire [24].

The primary caretaker or parent (n = 240) will complete measures on themselves and their child.

Teachers with a participating child in their class will complete a brief demographic form and a measure of teacher stress; Teacher sample size will be determined after recruitment of families.

Forty facilitators (teachers, or teachers partnered with classroom assistants), two from each school, will deliver the intervention to the children. The facilitators will be chosen by the school and will have undertaken relevant IY training to enable delivery.

Participant summary:

• 20 schools (10 in each phase)

• 240 children, 12 in each school, 6 intervention and 6 waiting list control

• 240 parents (primary caretaker of child participants)

• Teachers (of participant children, n = TBC following recruitment of families)

• 40 facilitators (teachers and classroom assistants)

See Additional File 2 for the Consort diagram of flow of participants.

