### Recruitment

Research staff will score the Teacher SDQs and inform schools of the initials and dates of birth of the highest scoring eligible children. School staff will initially approach the parents. If interested parents will sign a 'note of interest' form to include contact details and forward to the research team. The research team will telephone the parents to arrange a home visit to discuss the research and recruit the families.

Parents will consent for themselves and on behalf of their child. Consent will be sought at the initial home visit, which will be conducted in the parent's preferred language of Welsh or English. The information and consent forms are available in Welsh and English. The parent will have a week, if required, to decide whether to participate and will be encouraged to discuss participation with their partner, family and friends.

The information sheet also makes explicit that participants, having given their consent, will be free to withdraw their child and themselves from the study at any time without affecting future access to family or children's services. Confidentiality will be assured, unless the researcher has cause for concern regarding child protection issues.

Parents will be informed that their child will be chosen randomly as to whether they receive the intervention in the first or second year of delivery (intervention or waiting list control respectively).

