### Measures

Measures will be completed by teachers, parents, children and facilitators and collected by the research team. Demographic questionnaires will be completed by parents and teachers at baseline only. Primary and secondary measures will be administered at all time points.

*The primary outcome measure *is the Teacher SDQ, also used here as the screening measure. It is a 25-item inventory to assess the occurrence of particular behaviours that have been associated with conduct problems, hyperactivity, emotional symptoms, peer problems and pro-social behaviour in children aged 4-16. A high total difficulties score denotes higher occurrence of problematic behaviours [24].

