#### Secondary outcome measures

For children:

• The Eyberg Child Behaviour Inventory across all time points is a 36-item inventory, completed by the parent for the assessment of frequency and intensity of behavioural problems in children aged 2-16 years [25]. A high score in each of the subscales denotes more frequent/intense problem behaviour.

• The Bangor Dinosaur School Questionnaire has been developed by [name] [26], to assess levels of social and emotional competence. A high score denotes higher rates of social/emotional competence.

• The Wally Problem Solving test assesses children's problem-solving skills and solution types (positive and negative) in response to hypothetical problem situations http://www.incredibleyears.com.

• Blind observation of peer interaction to assess friendship skills (observation tool under development)

• Child interview to ascertain number of friends a child has

• Academic attainment - assessed by school records

• School attendance - assessed by school records

For parents (self-reports):

• The Parenting Scale questionnaire [27] is a 30-item inventory is designed to measure dysfunctional discipline practices in parents of children aged 1.5 to 4 years, but has been used successfully in older children up to age sixteen [8]. A high score denotes high rates of dysfunctional practices.

• The Beck Depression Inventory [28] is a 21-item measure to assess the severity of characteristic attitudes and symptoms associated with depression. A high score relates to increased levels of depression.

• The Warwick-Edinburgh Mental Well-being Scale (WEMWBS) [29] is a 14-item positively worded measure assessing mental health. The higher the score the higher the levels of well-being.

For teachers (self-report):

• The Teacher Stress Inventory (TSI) [30] is a 20-item measure to examine the effect of difficult classes, impolite pupils and maintaining class discipline on teacher stress levels. The higher the score the higher the stress levels.

Additional measures relating to programme delivery and child responsiveness consist of:

• Implementation fidelity checks - facilitator-completed after each week's session has been delivered

• Child Dina homework completion rates - facilitator assessed

• Attendance levels of child at Dina group - facilitator assessed

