### Randomisation

This is a pragmatic, parallel, RCT, with children individually randomised on a 1:1 basis, intervention or waiting-list control.

Individual (child) block randomisation within school will be applied with gender as the stratification variable. The North Wales Organisation for Randomised Trials (NWORTH), an independent registered trials unit, will perform the randomisation process using a computer programme written specifically for this trial. Randomisation will occur after eligibility has been established, informed consent obtained and baseline measures collected from parents.

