### Statistical analyses

Characteristics of the sample (child and parent) will be analysed and differences (if any) between the two conditions, intervention and control (and lost participants), will be recorded.

Demographic variables (e.g. parental status, ethnicity, education and income levels) will inform the mediator and moderator analysis - for whom the intervention worked best and why.

The main analysis is intention to treat (ITT), to include all participants regardless of protocol deviations and participant compliance or withdrawal, performed according to the assigned treatment group.

In addition to the ITT analysis a per protocol analysis will be conducted on data from participants who have remained in the study, attended at least one intervention session and have completed measures at each time point.

Different methods of dealing with missing data will be explored following data collection and establishment of how many and what type of missing values are achieved.

The difference between the intervention and control conditions on follow-up scores will be based on a mixed model analysis of covariance (ANCOVA), run on SPSS, of the response taking account of the random school effect, fixed treatment effect, gender, age/school year, and the baseline response value. Any similarities within the intervention group, due to participating in a group format intervention, will be controlled for in the model.

Effect sizes will be calculated using Cohen's (1988)[31] guidelines.

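### The primary ANCOVA adjusts for one outcome-related score although the trial collects another child-behaviour score before randomisation; pre-specifying it as a covariate would bring a modest gain in precision

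*Protocol article*

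**What the plan says.** **The model.** In the protocol article, Statistical analyses, follow-up scores are compared by a mixed-model ANCOVA with "random school effect, fixed treatment effect, gender, age/school year, and the baseline response value". One baseline value of the response is the only outcome-related term.

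**The outcome and the selection score.** Under Measures, the primary outcome "is the Teacher SDQ, also used here as the screening measure". Under Participants, the children are those "identified as scoring at least borderline for concern on the total difficulties score of the Teacher Strengths and Difficulties Questionnaire", and under Recruitment the schools are told of "the highest scoring eligible children".

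**What else is collected.** Measures adds: "Primary and secondary measures will be administered at all time points". Secondary outcome measures includes a parent rating: "The Eyberg Child Behaviour Inventory across all time points is a 36-item inventory, completed by the parent".

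**Timing.** Under Randomisation: "Randomisation will occur after eligibility has been established, informed consent obtained and baseline measures collected from parents". Teacher and child baseline measures are not mentioned there, and under Blinding teachers are not blind to condition. The article does not say whether the baseline Teacher SDQ is the screening form itself or a later rating.

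**The concern.** A covariate measured before allocation that predicts the outcome narrows the confidence interval for the treatment effect without biasing it. This trial has at least one such score beyond the one it uses, and the stated covariate list leaves it out. What is at stake is the width of the interval for the primary comparison. Neither its validity nor the direction of the estimate is in question.

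The point draws attention here because children are selected on the same instrument that supplies the single covariate. In the selected sample, that score will explain a smaller share of the follow-up variance than it would among all pupils.

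**Working it through.** **The plan's own figure.** Sample size and power calculation gives 88% power for N = 160 at the 5% level, with no effect size. Assume d = 0.5, two-sided. The noncentrality is N·d²/4 = 160 × 0.25/4 = 10. The normal approximation gives Φ(√10 − 1.96) = Φ(1.20) = 0.885, and the F test for a 2 × 20 factorial (1 and 120 df) gives 0.880. The 88% thus fits d = 0.5 with no covariate in the calculation, so it does not depend on this point.

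**Assumptions (none is in the article).** Scores are normal with unit variance among all pupils. S is the screening SDQ, B a later baseline SDQ, Y the follow-up SDQ and P the parent Eyberg score. Selection keeps the top 20-35% on S, which cuts the variance of S to k = 0.219 (top 20%) or 0.288 (top 35%).

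**Step 1: does selection cost adjusted precision?** Take r(S,Y) = 0.7 and the top 20%.
- Variance of Y in the selected sample: 1 − 0.49 × (1 − 0.219) = 0.617.
- Part explained by S: 0.49 × 0.219 = 0.107, or 17% of 0.617, against 49% unselected.
- Residual variance: 0.617 − 0.107 = 0.510, the same as 1 − 0.49 without selection.

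The share explained falls, but the outcome's own spread falls with it. The adjusted standard error in SDQ points is unchanged.

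**Step 2: adding S to a later baseline B.** Covariances in the selected sample are c(i,j) = r(i,j) − r(i,S)·r(j,S)·(1 − k). With all three correlations at 0.7 and the top 20%:
- Var(B) = Var(Y) = 0.617 and Cov(B,Y) = 0.7 − 0.49 × 0.781 = 0.317.
- Residual given B: 0.617 − 0.317²/0.617 = 0.454.
- Residual given B and S: 0.51 − (0.7 − 0.49)²/0.51 = 0.424.
- Reduction: 1 − 0.4235/0.4542 = 6.8%, equivalent to 240 × (0.4542/0.4235 − 1) = 17 more children.

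| Assumed correlations | Reduction in residual variance, top 20% to top 35% |
|---|---|
| All 0.6 | 4.7-6.0% |
| All 0.7 | 6.8-8.3% |
| All 0.8 | 9.7-11.5% |
| S-B 0.8; both 0.6 with Y | 2.8-3.4% |
| S-B 0.8; both 0.7 with Y | 5.0-5.9% |
| S-B 0.9; both 0.6 with Y | 1.8-2.0% |
| S-B 0.9; both 0.7 with Y | 3.1-3.5% |
| S-B 0.8; S-Y 0.5; B-Y 0.6 | 0.1% |

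The last row shows that the gain nearly vanishes if the earlier rating predicts follow-up less well than the later one.

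**Step 3: adding Eyberg to a single Teacher SDQ.** The proportional reduction is [r(P,Y) − r(P,S)·r(S,Y)]² / {[1 − r(P,S)²]·[1 − r(S,Y)²]}. Assume that repeat teacher ratings would correlate 0.6-0.8, that a parent score correlates 0.2-0.4 with the teacher's, and that every correlation with follow-up is 0.85 of its value at screening.
- Upper end: r(P,S) = 0.4, r(S,Y) = 0.6 × 0.85 = 0.51, r(P,Y) = 0.34. This gives (0.34 − 0.204)²/(0.84 × 0.740) = 3.0%.
- Lower end: r(P,S) = 0.2, r(S,Y) = 0.8 × 0.85 = 0.68, r(P,Y) = 0.17. This gives (0.17 − 0.136)²/(0.96 × 0.538) = 0.2%.

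A simulation truncated on S gave the same range, 0.2% to 2.9%. Without the fading over time, the most favourable case (r(P,S) = r(P,Y) = 0.4, r(S,Y) = 0.6) gives (0.4 × 0.4)²/(0.84 × 0.64) = 4.8%.

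**Step 4: effect on power.** Assume N = 160, d = 0.5 and a first covariate correlating 0.4 with the outcome. Power is 93.2%. A second score that removes 1%, 4% or 9% of residual variance raises it to 93.4%, 94.1% or 95.1%.

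**The case against.** The strongest reply is that nothing here is wrong. ANCOVA on the baseline response with school, sex and age is a standard and valid primary analysis. The Statistical summary announces adjusted analyses, so the list need not be exhaustive, and extra covariates are often left to an analysis plan that is not shown. A second Teacher SDQ may not exist: one form serving as both screen and baseline is a natural reading, and the larger gains then disappear. The size rests on correlations that the article does not give.

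Most of this stands, and it keeps the point minor. It does not remove it. The article does state the terms of its primary model, and that model leaves out a child-behaviour score that the article itself places before randomisation.

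Two stronger readings are tempting and are not supported:
- *Selection on the Teacher SDQ has cost the trial precision, which a second score would restore.* Step 1 shows no such loss under a linear model. A second score adds information; it does not repair damage.
- *Any other baseline score would serve, for instance the Bangor Dinosaur School Questionnaire.* The article does not say who completes it or that it precedes allocation. If an unblinded rater completed it after allocation, adjusting for it could introduce bias.

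**Conclusion.** The primary analysis uses less prognostic information than the trial collects before randomisation. It remains valid, and unbiased provided the baseline Teacher SDQ precedes allocation, which the article guarantees only for the screening rating.

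The available gain is modest. It is roughly 0-12% of residual variance if a separate screening SDQ is added to a later baseline SDQ. At 12% the standard error is multiplied by √0.88 = 0.94. The gain is about 0-3% if Eyberg is added to a single SDQ; at 3% the multiplier is √0.97 = 0.985. Both ranges depend on assumed correlations, normality and linearity. The upper end of the first also needs the screening rating to predict follow-up as well as the later baseline does, and the two pre-intervention ratings to agree no better with each other than with follow-up.

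**What to change.** In Statistical analyses, for the Teacher SDQ outcome, say which rating is the baseline value and name one additional covariate known to precede randomisation:
- if screening and baseline are separate ratings, include the screening Teacher SDQ total alongside the baseline Teacher SDQ total, and confirm that the latter is also taken before allocation;
- if one form serves both purposes, include the parent-rated baseline Eyberg score, naming the subscale;
- do not use the Bangor questionnaire unless it is shown to be completed before allocation.

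Fix the choice, and a rule for missing values of the added covariate, before any follow-up data are seen. The cost is a line of wording, one degree of freedom and the missing-value rule. No new data collection is needed.

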#### Statistical summary

Statistical analyses, including subgroup analyses and adjusted analyses, indicating those pre-specified and those exploratory will be conducted to include (amongst others):

• Sample characteristics

• ANCOVA will establish differences between conditions & across time points

• Effect sizes will be calculated using Cohen's d

• Mediator & moderator analyses will establish whom the intervention works best and why

• Regression analyses & correlations will assess scores on a measure predicting, or having a relationship, with another

## Discussion

This trial will provide important information on the delivery and effectiveness of a child centred intervention delivered in small groups of children, at risk of developing more severe conduct problems, in school settings by school staff. The effects on child behaviour in school and home environments, academic attainment, peer interactions, parent and teacher mental health, will be assessed.

A number of challenges exist in carrying out the proposed study; the biggest challenge is that of parental engagement and consent. The parents will initially learn of the trial through school staff. It is important that school staff are fully aware of the details of the study and are fully briefed with the most effective means of presenting the trial to parents in the most positive light to ensure that parents do not feel stigmatised, or in any way to blame for their child's social, emotional, or behavioural difficulties. Individual meetings with the Principal Investigator, Head Teachers and proposed facilitators will serve to brief school staff and alleviate any concerns on engaging with parents. Staff will be given information sheets and a template letter, summarising the study, to give to parents to aid discussion. Parents will mainly be approached on a one to one basis during parents' evening at school. School staff will help parents complete a 'note of interest' form with contact details and child details to be sent to the research staff to enable initial contact to be made. Parents will be encouraged to contact the research team or school staff with any queries.

Teachers will receive training to deliver the programme as part of the trial. Teachers will be required to take video recordings of their session delivery to monthly group supervision, undertaken by an IY Mentor. To overcome possible reticence of showing the recordings teachers will choose which sections of the recording to show at supervision for discussion, for example a section of the session that they were proud of, or a section of a session that they felt could have gone better to receive guidance and feedback on.

Despite these, and other, possible challenges the strength of the trial lies in the fact that three main elements when evaluating a complex intervention, as outlined by the MRC will be included, namely the assessment of process, implementation and outcomes [32].

### Ethics and research governance

The trial is conducted in compliance with the principles of the Declaration of Helsinki (1996) and the principles of Good Clinical Practice (GCP).

The study protocol and other documentation have been approved by North Wales Research Ethics Committee (REC), and School of Psychology, Bangor University REC. Any subsequent protocol amendments will be submitted to the RECs for approval.

Both RECs will be provided with progress reports and a final study report The Charity and University's lone worker, child protection and safeguarding policies will be adhered to.

### Data management, protection and confidentiality

Data will be handled in accordance with the Data Protection Act (1998). Databases with personal, identifiable information will be password protected on multiple levels and stored on a secure server. Statistical databases will hold non-identifiable data. All questionnaires will be inputted at the item level.

Twenty percent of inputted data will be checked to assess input error rates. Participant identifiable data is to be shared only within the research team on a need-to-know basis.

Confidentiality will be maintained and no one outside the trial team will have access to the database. The completed non-identifiable questionnaires will be stored in a locked cabinet at the University.

The trial database is securely held and maintained on the University's research data protection server, which is regularly backed up.

### Publication

The trial results will be written up for submission to a peer reviewed journal. No data relating to individuals will be identified in any publication.

